7. Although the frequency of use has been reduced according to the protocol, it is difficult to use even if the lower limit (less than 70% of the total planned number of uses) is reached.	
8. Who became pregnant.	
9. Poor compliance (if it is judged that less than 70% of the total planned number of uses will be used).	
10. Who cannot receive intervention due to hospital transfer.	
11. The entire study was discontinued	
12. For other reasons, the doctor judged it appropriate to discontinue the study.

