### Endpoints

#### Primary endpoint

The primary endpoint is the mean and standard deviation (SD) for changes from baseline in the upper limb FMA at week 2. In addition, the effectiveness of this treatment will be examined by comparing the calculated mean value with 3.0, which is estimated as the amount of change in the case of conventional treatment. The FMA scale was developed as the first quantitative evaluative instrument for measuring sensorimotor stroke recovery in patients with hemiplegic stroke. The FMA is an efficient clinical examination method that has been widely tested in stroke populations. Its primary value is the 66-point motor domain, which has received the most extensive evaluation of upper-limb function [14]. The change in the FMA score can be used to evaluate the degree of cancelation of synkinesis. FMA has the advantage of being able to capture the patient’s overall picture and making it easier to predict the effects of rehabilitation [15, 16]. FMA has been reported to correlate with the degree of independence in activities of daily living [17]. In Japanese hospitals, the general length of stay in an acute care hospital is around 2 weeks; therefore, the timing of the endpoint was planned. We planned to conduct a subgroup analysis to adjust for the number of trials after this study.

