#### Secondary endpoint

For each endpoint (points 1-6 provided below), we will perform the same analysis as the primary endpoint at each evaluation time point after starting treatment from baseline.Change in upper limb BRS at weeks 2 and 4,Amount of change in Functional Independence Measure (FIM) at weeks 2 and 4,Change in upper limb FMA at weeks 1, 3, and 4,Amount of change in BI at weeks 2 and 4,Amount of change in grip strength at 1, 2, 3, and 4 weeksUpper limb manual muscle strength test: the amount of change in manual muscle test (MMT) at weeks 1, 2, 3, and 4.

For implementation compliance, the treatment implementation status for each day will be aggregated.

The BRS classifies the recovery process into six stages. This classification, established from clinical observations of many hemiplegic patients, is based on the degree of spasticity, synergy, and voluntary movement. A previous study reported that this classification of BRS has face validity, but it has never been assessed for reliability and validity [18]. In clinical practice, BRS is used for simple evaluation of motor paralysis, but FMA is used for more detailed evaluations. FMA is rated higher than BRS for its validity and reliability. Therefore, for the purpose of this study, we will be using both outcome measures.

The BI, which is used as a simple and useful evaluation of a patient’s independence, can be accurately and quickly scored by adhering to the definition of 10 items concerning ADL, with a score range of 0–100. The FIM is considered more valid than BI and equally reliable in the assessment of disability [19]. The FIM was developed for precise evaluation of ADL [20] and is divided into two sections: a motor section, which includes 13 items, and a cognitive section, which includes 5 items. Each item is graded from 1 (totally dependent) to 7 (completely independent), and the total FIM score range is 18–126. BI scores have been closely correlated with FIM [21]. Both will be used in this study because of the limitations of using only one assessment of ADL.

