### Sample size

Since this is an exploratory study, the target number of cases is set at 20 from the feasibility viewpoint. At this time, if the average ± SD of the change amount of the main endpoint upper-limb FMA is estimated to be 6.0 ± 2.0, with reference to a previous report [22], the width of the 95% confidence interval of the change amount is approximately 1.9. As the amount of change in the case of normal treatment is expected to be 3.0 ± 1.0, it is considered that the effect of this treatment can be sufficiently confirmed.

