#### Statistical analysis plane

The primary endpoint is the change in the amount of upper-limb FMA from baseline to week 2. For efficacy evaluation, the full analysis set (FAS) and per-protocol set (PPS) will be used. The FAS is defined as the patient population excluded from the SS for any of the following reasons: ineligible cases after enrolment and cases with no data related to efficacy at any time after the start of study treatment. The PPS is defined as the patient population excluded from the FAS for any of the following reasons: violation of safety-related exclusion criteria, met criteria for study discontinuation, violation of effectiveness-related inclusion criteria, use of prohibited treatment, study rehabilitation compliance rate < 70%, or treatment period < 1 week.

Concerning the primary and secondary endpoints, the degree of improvement in parameters before and after intervention will be compared using the paired *t* test with a significance level of 0.05 and a tendency level of 0.10, and the improvement will be estimated using 95% CI. If the improvement in FMA between before and after the intervention is ≤ 0.10, we will proceed to the next pivotal clinical trial. Similarly, we will consider progression to the next trial if the BRS, FIM, grip strength, and BI values are ≤ 0.10. Missing values in the efficacy analysis will be supplemented with the immediately preceding value (last observation carried forward). We will analyze covariance with the intervention value as a covariate, and calculations will be performed using Statistical Package for the Social Sciences 22.0J (SPSS Japan, Tokyo, Japan).

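### LOCF is the only stated missing-data method in patients who are still recovering, so full-analysis-set mean changes are liable to bias, most of all at week 4

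*Protocol article*

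**What the plan says.** The Statistical analysis section (subsection *Statistical analysis plane*) states: "Missing values in the efficacy analysis will be supplemented with the immediately preceding value (last observation carried forward". It names no other method and no sensitivity analysis for missing data. Efficacy is analysed in a full analysis set (FAS) and a per-protocol set (PPS). The FAS drops patients with no efficacy data after the start of treatment. The PPS also drops those who met a discontinuation criterion or whose compliance was below 70%.

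Other parts of the article bear on this choice:

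- **Recovery.** Table 1 admits patients up to 1 month after the event, and the Background puts the improvement period at 3 months.
- **Stay.** The Primary endpoint section explains the week-2 time point: "the general length of stay in an acute care hospital is around 2 weeks; therefore, the timing of the endpoint was planned". Treatment and the secondary endpoints run to week 4.
- **Transfer.** Table 1 lists as a discontinuation criterion: "Who cannot receive intervention due to hospital transfer".
- **Visits.** Upper-limb FMA is measured at weeks 1, 2, 3 and 4. FIM is measured less often: "Amount of change in Functional Independence Measure (FIM) at weeks 2 and 4". BRS and BI follow the same two visits.
- **Benchmark.** The week-2 mean change is compared with a fixed 3.0, the change expected under conventional treatment.

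**The concern.** LOCF assumes that a patient's score stops changing at the last visit attended. The article's own account is that patients go on improving through all 4 weeks. A carried value is then too low, and a single arm set against a fixed number has no control group in which the same error could cancel.

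The article also shows how values may go missing. A 4-week course outlasts the usual stay, and a transfer that prevents the intervention ends study treatment. Weeks 3 and 4 are the most exposed. Week 2 is less exposed because it was chosen to fit the stay, although its clock starts at treatment and not at admission.

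FIM, BRS and BI have no week-1 visit. A patient with a week-1 FMA stays in the FAS. If that patient's week-2 FIM is missing, the value carried is the baseline, and the change is exactly zero. These scales also enter the decision to proceed to the next trial.

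The direction is not guaranteed. A patient stopped for exacerbation (Table 1, discontinuation criteria 4 to 6) may keep a score taken before the worsening, which biases the mean upward.

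**Working it through.** **Inputs from the article (Sample size).** Number of patients: "the target number of cases is set at 20 from the feasibility viewpoint". Week-2 FMA: "the change amount of the main endpoint upper-limb FMA is estimated to be 6.0 ± 2.0". Benchmark: "the amount of change in the case of normal treatment is expected to be 3.0 ± 1.0". Precision: "the width of the 95% confidence interval of the change amount is approximately 1.9".

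**Step 1. The plan's own figure.** Full width = 2 × t(0.975; 19) × SD/√n = 2 × 2.093 × 2.0/√20 = 1.87. This agrees with the stated 1.9 and presumes that all 20 patients are observed.

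**Step 2. Bias formula.** With a fraction m missing at random and the previous visit carried forward:

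LOCF mean = true mean − m × (true mean − mean at last visit).

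**Step 3. Week 2.** Assumptions: week-1 mean 3.0 (linear gain), week-1 SD 1.4, correlation 0.8 between weeks. Means follow from step 2, for example 6.0 − 0.2 × 3.0 = 5.4. Coverage and widths come from 20,000 simulated trials of 20 patients.

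| Missing | LOCF mean | 95% CI coverage | LOCF width | Observed-only width |
|---|---|---|---|---|
| 10% | 5.7 | 91% | 1.98 | 1.97 |
| 20% | 5.4 | 79% | 2.08 | 2.11 |
| 30% | 5.1 | 62% | 2.13 | 2.30 |
| 50% | 4.5 | 22% | 2.11 | 2.91 |

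With complete data the simulated width is 1.85.

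**Step 4. Why coverage falls.** Mixing carried and observed values adds variance: m(1 − m) × gap² + (1 − m) × SD₂² + m × SD₁². At 20% this is 0.16 × 9 + 0.8 × 4 + 0.2 × 1.96 = 5.03, an SD of 2.24 against 2.0. The interval is therefore wider than with complete data. Its centre has moved by 0.6, which is 0.6/(2.24/√20) = 1.2 standard errors, and that shift accounts for the lost coverage. At 30% the variance is 0.21 × 9 + 0.7 × 4 + 0.3 × 1.96 = 5.28, the standard error is 0.51, and the shift is 0.9/0.51 ≈ 1.75 standard errors.

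**Step 5. Week 4, with week 2 carried forward.** Assumptions: week-2 mean 6.0; week-4 SD 2.5 (true mean 8) or 2.8 (true mean 10 or 12); correlation 0.8 per week. Each cell gives the LOCF mean and the coverage.

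| Assumed true week-4 mean | 10% | 20% | 30% | 50% |
|---|---|---|---|---|
| 6 (plateau) | 6.0; 95% | 6.0; 95% | 6.0; 95% | 6.0; 95% |
| 8 | 7.8; 94% | 7.6; 89% | 7.4; 82% | 7.0; 59% |
| 10 | 9.6; 91% | 9.2; 81% | 8.8; 63% | 8.0; 25% |
| 12 (linear) | 11.4; 89% | 10.8; 72% | 10.2; 49% | 9.0; 10% |

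**Step 6. Effect on the tests.** At 30% missing in week 2, the distance from zero is 5.1/0.51 = 10 standard errors, and the distance from 3.0 is 2.1/0.51 = 4.1. In the simulation the lower 95% limit still exceeds 3.0 in 97.9% of trials at 30% missing and in 82% at 50%.

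**Step 7. The PPS.** A patient who leaves at week 2 has had about 10 of 20 sessions, or 50%. That is below the 70% limit, so this patient is out of the PPS on compliance as well as on discontinuation.

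**The case against.** Much can be said for the plan. The study is exploratory, and its Discussion gives feasibility and safety as the main objectives. The bias calculated here is downward, hence conservative for efficacy. The progression rule rests on a before/after test, which for FMA hardly moves. The PPS removes most patients whose values would be carried, and an analysis plan not shown may hold sensitivity analyses. All this limits the consequence. But the PPS is a selected group and does not repair the week-4 estimate: the FAS fills those patients in and the PPS leaves them out. And LOCF is a method the article states, not a detail it leaves open.

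Three stronger readings are tempting, and the article does not support them.

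- *LOCF makes the intervals falsely narrow.* Not in general. In these scenarios they are about as wide as with complete data, or wider. Against observed cases only, they are narrower at high missing rates (2.11 against 2.91 at 50% in week 2) but wider under steep recovery (3.32 against 2.95 at week 4, true mean 12, 20% missing).
- *Transfer at 2 weeks ends participation.* This joins two separate statements. The stay is a general figure, the criterion covers only transfers that prevent the intervention, and nothing says that assessments then stop.
- *The results will be biased.* No missing rate is given, and a plateau after week 2 would leave no bias at week 4.

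**Conclusion.** The point holds with moderate confidence and should be acted on. LOCF as the sole stated method does not fit a population described as still recovering, and FAS mean changes are liable to bias. Exposure is greatest at weeks 3 and 4 and for the two-visit scales, and smaller at the primary week-2 time point.

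Under linear gain to week 2, each 10% missing costs 0.3 points. At 20% or 30% missing, the planned 3-point excess over 3.0 shrinks by 20% (0.6/3) or 30% (0.9/3). At week 4 the loss for each 10% missing is 0.2 to 0.6 points for assumed true means of 8 to 12. With 30% missing, coverage is about 82, 63 and 49% for true means of 8, 10 and 12.

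All missing rates, the week-1 and week-4 means and SDs, the correlation and random dropout are assumptions. Upward bias from patients stopped for exacerbation is possible but cannot be sized from the article. What is at stake is the size of the estimated effect that the next trial would inherit, more than whether the FMA test is significant.

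**What to change.** In the *Statistical analysis plane* subsection, replace LOCF as the main FAS method:

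1. **FMA.** Fit a repeated-measures mixed model to all observed changes at weeks 1 to 4, with visit and baseline FMA as terms and an unstructured covariance. State in advance the simpler structure to use if it does not converge. Read the week-2 mean and 95% CI from the model at the mean baseline, and compare with 3.0.
2. **Other endpoints.** Use the same model for grip strength. For FIM and BI, use a baseline-adjusted likelihood or multiple-imputation analysis. Report BRS, a six-stage scale with two visits, on observed data. State which of these routes applies to MMT.
3. **Sensitivity.** Keep LOCF. Add an analysis that sets change to zero for patients stopped for exacerbation, since the mixed model does not by itself address loss that depends on unseen worsening.
4. **Reporting.** Give the number observed at each visit for every endpoint.

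Cost: a little more analysis work and no new visits. An unstructured covariance over four visits has 10 parameters, which is a lot for 20 patients, hence the pre-stated fallback.

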#### Safety assessment

We will create a list of adverse events (AE) and calculate the frequency and rate of occurrence. AE will be collected for safety analysis. AEs are defined as any unfavorable or unintended sign, symptom, or disease, including abnormal laboratory values. Serious AEs include death, adverse events requiring hospitalization or prolonged hospitalization, life-threatening adverse events, and adverse events resulting in permanent or significant disability or defects. Other serious medical events based on good medical judgment may also be considered serious AEs when the patient's health is at risk and intervention is required to prevent the mentioned consequences. The safety analysis set (SS) will include patients with safety evaluation data after starting study treatment.

#### Data monitoring

All data will be stored in a database in a locked cabinet at the laboratory of the Department of Rehabilitation Medicine at Nara Medical University. The assessors will enter the data into the database system. Trial enrolment and duration will be regulated to ensure the robustness of the data.

#### The quality and safety of monitoring

Safety monitoring of this trial will be conducted by an independent physician with relevant expertise once a month. All participants and visits will be monitored by a third party.

On the other hand, the auditors will inspect several times during the period.

To increase the reliability of the evaluation, one neurological professional will perform all assessments in this study.

#### Confidentiality

All personal information about potential and enrolled participants and proxies will be stored in a manner the third party cannot access.

## Discussion

We planned this study to evaluate the effect of FES, a low-frequency treatment device, on the cancellation of synkinesis in patients with incomplete paralysis due to cerebrovascular accidents. Withdrawal from synkinesis is important for the recovery of motor paralysis, and in addition to conventional rehabilitation, canceling synkinesis using FES will likely facilitate recovery of motor paralysis in patients with moderate hemiplegia due to cerebrovascular accidents. The mechanism of FES is based on the principles of neuroplasticity [22, 23]. The recovery of motor function depends on the integrity of the neural network in the cortex of the damaged hemisphere. This is probably attributed, in part, to the temporal dynamics of corticomuscular interactions in post-stroke recovery. Especially, the changes in corticomuscular interaction are more obvious in the acute stage of stroke than in the chronic stage [24].

Since synkinesis does not appear in patients with complete paralysis with a BRS of 1 but does appear in patients with incomplete paralysis with an upper limb BRS of 2–4, we planned this cohort for enrolment. We will evaluate the usefulness of the IVES+ medical device in patients with a BRS of 2–4 using a novel method to cancel synkinesis in the early phase of cerebrovascular disorders. The level of global synkinesis intensity in the paretic arm is related to the functional outcome of patients with post-stroke hemiparesis and is particularly dependent on elbow flexor muscle contractions [25, 26]. Therefore, we will use the FES to perform dorsiflexion of the wrist when the elbow is flexed.

In this exploratory study, we will evaluate the usefulness of the medical device IVES+ for canceling global synkinesis and recovery from motor paralysis in patients with moderate hemiplegia caused by cerebrovascular disorders. This study also explores whether improved global synergy is associated with improved hand impairment. This study has the following limitations: it is a single-arm study with a short observation period and a small number of planned patients, but the result from this study will be useful for the next validation research. The main objectives of this exploratory clinical trial are feasibility and safety. Efficacy is not based on inter-group comparisons but on evaluating response or maintenance in individual cases. The selected population can be very large in studies like this, and the sample may vary. Therefore, it is necessary to perform a subgroup analysis, such as disease type, severity, or age of onset. However, due to our small sample size, our study may not have sufficient power for this analysis. As this analysis may not have sufficient power, the results should be interpreted cautiously. Contrarily, it may be possible to infer efficacy by performing a compliance analysis based on the number of treatments.

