## Methods

### Design

Reporting was in accordance with the checklist for pilot and feasibility trials [13]. This single-arm study was designed to explore the feasibility and clinical usefulness of a novel low-frequency device for canceling global synkinesis in patients with incomplete paralysis and cerebrovascular disorders (Fig. 1). In this study, Fugl-Meyer Assessment (FMA) will be used to evaluate the degree of synkinesis cancelation. FES has been used in conventional treatments to induce and enhance muscle contraction; however, in this study, FES will be used for patients with incomplete paralysis, defined as upper-limb Brunnstrom stages (BRS) 2–4, caused by a cerebrovascular accident. Eligible participants are patients aged ≥ 20 years with moderate hemiplegia caused by a cerebrovascular accident. The inclusion and exclusion criteria are listed in Table 1. Qualified patients will undergo a novel rehabilitation program using a low-frequency treatment device and regular rehabilitation for 4 weeks (Table 2).

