**Fig. 2 Fig2:**
[figure not shown]
Difference between conventional application and FRAT application of IVES+. The conventional application of this device for motor paralysis is only direct stimulation, in which the lead-out and stimulation electrodes are placed on the same muscle. In this FRAT study, a lead-out electrode was placed on a muscle capable of voluntary contraction, and its contraction was monitored. Subsequently, a stimulation electrode was placed on an antagonistic muscle against a muscle that causes synkinesis

The distinctiveness of this intervention is that it is not primarily intended for strengthening muscles. Instead, it is used to retrain the neuromuscular system to execute tasks that cannot be performed voluntarily. The patients will undergo the novel FES training 20 min a day for 5 days, for 4 weeks, for a total of approximately 20 sessions, and the number of repetitions will be determined based on individual participants’ strength and endurance. The number of standard rehabilitation sessions is, in principle, fixed for all subjects but varies depending on the condition.

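### The number of treatments received depends on the patient's course, so its association with FMA change cannot show efficacy in this single-arm trial

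*Protocol article*

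**What the plan says.** The Discussion recommends subgroup analyses, concedes that they may be underpowered and asks for caution. It then sets one analysis apart from that caution: "it may be possible to infer efficacy by performing a compliance analysis based on the number of treatments". The same section says of efficacy: "Efficacy is not based on inter-group comparisons but on evaluating response or maintenance in individual cases". The Primary endpoint section adds: "We planned to conduct a subgroup analysis to adjust for the number of trials after this study".

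The design has one arm (Design section: "This single-arm study was designed to explore the feasibility and clinical usefulness of a novel low-frequency device"). The Intervention section plans 20 minutes a day, 5 days, for 4 weeks, "for a total of approximately 20 sessions". It says separately that "the number of repetitions will be determined based on individual participants’ strength and endurance", and that standard rehabilitation is fixed in principle but may vary with the patient's condition.

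The discontinuation criteria in Table 1 end participation for, among other reasons, worsening of the primary disease, complications, illness, intolerance even after use has been reduced, expected use below 70% of plan, hospital transfer, and complete cure. The section headed Statistical analysis plane fills missing efficacy values by last observation carried forward (LOCF).

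**The concern.** Everyone is planned to receive the same number of sessions. Differences in the number received are neither assigned by design nor random. They arise after baseline, and several of the listed reasons are themselves signs of how the patient is recovering. Relating FMA change to sessions received then mixes any device effect with prognosis, with reverse causation and with the time at which the last FMA was taken.

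The Discussion presents this analysis as a way round low power, but the obstacle is confounding, which more patients would not remove. With no control group, a dose-response pattern could look like the most persuasive evidence of efficacy in the report while having no causal content. A flat or negative pattern would be just as hard to read.

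**Working it through.** **1. Inputs from the document.** n = 20; expected change 6.0 ± 2.0 with the device and 3.0 ± 1.0 with normal treatment (Sample size); about 20 sessions over 4 weeks (Intervention); primary FMA at week 2; LOCF. The article gives no figure for the compliance analysis. The one related figure, the confidence interval width, reproduces: 2 × t(0.975, 19) × SD/√n = 2 × 2.093 × 2.0/√20 = 1.87, stated as about 1.9.

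**2. Timing.** Sessions planned before the week-2 assessment: 5 × 2 = 10. Sessions planned in total: 5 × 4 = 20. About half of the course comes after the primary outcome and cannot have caused it. The 70% limit is 0.70 × 20 = 14 sessions over the full course, so the per-protocol set spans only about 14 to 20.

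**3. What moves the count.**

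| Reason (Table 1) | Likely link with recovery |
|---|---|
| Worsening, complications, illness | fewer sessions, poorer recovery |
| Reduced frequency, poor compliance | fewer sessions; may follow tolerance and condition |
| Complete cure | fewer sessions, best recovery |
| Hospital transfer | direction not stated |

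The reasons do not all push the same way.

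**4. Illustration: shared prognosis, inert device.** 40,000 simulated trials of n=20, change 3.0 ± 1.0, device effect zero. Sessions were about 18 ± 2, rounded and limited to 10–20. A latent capacity has correlation a with sessions and b with recovery. The test was two-sided, so 2.5% is expected in each direction. The session distribution, a, b and the cure share are assumptions.

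| Scenario | Mean r | Positive, p<0.05 | Negative, p<0.05 |
|---|---|---|---|
| a=b=0 | 0.00 | 2.5% | 2.4% |
| a=0, b=0.6 | 0.00 | 2.4% | 2.6% |
| a=b=0.3 | 0.09 | 5% | 1% |
| a=b=0.5 | 0.24 | 17% | 0.1% |
| a=b=0.7 | 0.46 | 58% | 0% |
| a=b=0.8 | 0.61 | 86% | 0% |
| a=b=0.5, best 10% stop early as cured | −0.26 | 2% | 28% |
| a=b=0.7, best 10% stop early as cured | −0.13 | 6% | 16% |

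**5. Illustration: LOCF alone, inert device.** Assume linear recovery and patients who stop at random after week 1 with 5 sessions and are not assessed again. Their carried-forward change averages 3.0/2 = 1.5 instead of 3.0, a gap of 1.5 points. With completers at 17–20 sessions, a positive association at p<0.05 appeared in 17% of trials with one such patient, 46% with two and 69% with three, against 2.6% with none. No prognostic confounding is needed. Counting only sessions before week 2 does not remove this link, since such a patient still has 5 sessions against about 10 planned.

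**The case against.** The strongest reply is that the sentence is a hedged Discussion remark. It is not in the Statistical analysis plane section and plays no part in the progression rule. For compliance, the Secondary endpoint section promises only to aggregate daily implementation. The article calls the study exploratory, puts feasibility and safety first, and lists the single arm as a limitation. All of this is correct and limits the consequence. It does not correct the inference: the caution is attached to the subgroups, the compliance analysis is set against them, and confounding is not mentioned.

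Three stronger readings are tempting and are not supported.

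- A reader might infer that strength and endurance set the amount of treatment being analysed. The Intervention section ties them to repetitions within sessions, whereas the Discussion's analysis concerns the number of treatments. The route to that number is reduced frequency and the discontinuation criteria.
- A reader might infer that a positive dose-response would necessarily appear with an inert device. The cure criterion pushes the other way, and no spurious slope appears if session count is unrelated to recovery.
- A reader might take the simulated percentages as estimates for this trial. They show what follows from assumed correlations; no document figure fixes those correlations.

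The Primary endpoint sentence on adjusting for the number of trials is also unclear. Reading it as adjustment of the primary result for treatments received is an interpretation.

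**Conclusion.** The point holds in a limited form. An association between number of treatments and FMA change could arise, in either direction, without any device effect, so the compliance analysis cannot support an inference of efficacy. This rests on the single arm, the common planned number of sessions and the listed reasons for receiving fewer, all of which are in the article. The LOCF mechanism needs one further assumption: that some patients who stop early are not assessed afterwards.

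The size is unknown. The range of 5% to 86% for a spurious positive result at p<0.05, and the reversed average sign in the two cure scenarios, depend wholly on assumed inputs. The primary analysis and the progression rule are unaffected by the remark as written; what is at stake is one efficacy claim that the report might make.

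**What to change.** - Delete the Discussion's statement that efficacy may be inferred from the number of treatments, and label that analysis descriptive.
- If an association with week-2 FMA change is shown, count only sessions before the week-2 assessment and state beside the result that it does not support a treatment effect.
- Do not adjust the primary result for the number of treatments received, and reword the Primary endpoint sentence on the number of trials so that it cannot be read that way.

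Covariate adjustment is not a substitute. It is fragile with 20 patients, and baseline variables cannot remove reverse causation that arises after baseline.

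The cost is wording only: no new data or patients, and one exploratory efficacy claim is given up.
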